### Setting

This Nordic multicentre study is a collaboration between gastroenterology departments in 11 Nordic hospitals (online supplemental appendix 1). The study enrolment will occur between 7 February 2022 and 31 December 2023. The first patient’s first visit was conducted in Oslo University Hospital in February 2022, and the first patient’s last visit was in February 2023. All inclusion sites will conduct their last patient’s first visit and last patient’s last visit in December 2023 and December 2024, respectively.

10.1136/bmjopen-2023-083144.supp1Supplementary data

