### Statistical methods

Referring to earlier studies, approximately 40% of a population referred with suspected IBD will have the diagnosis confirmed according to the ECCO criteria (or comparable).^5 31^ Cost and practical issues will restrict the sample size to approximately 800 patients, with an expected 80% participation rate.

In the *diagnostic test accuracy study*, we will compare two independent binomial proportions, using the likelihood ratio (LR) statistic with a χ^2^ approximation and two-sided significance level (0.05). With an expected sample size of 640 participants (assuming a biomarker positivity-to-negativity ratio of 1 to 1), we will reach an approximate statistical power of 100%, assuming that the proportion of patients diagnosed with IBD is 80% in the biomarker positive group and 20% in the biomarker negative group. If we include 640 study participants, we will potentially (‘rule of thumb’) be able to build a multivariable statistical model with as many as 64 covariates. Thus, we will examine a variety of biochemical variables for diagnosing IBD (see Biomarkers section). The expectation is that a proportion of 100–200 preliminary biomarkers will be evaluated in this model to distinguish non-diagnostic markers and preliminary biomarkers that can be replicated. When applying a significance level of 0.05, each biomarker has a 5% risk of being replicated by chance. Thus, in the evaluation of, for example, 100–200 biomarkers, five to 10 biomarkers may be replicated by chance. In contrast, the risk of not replicating ‘true’ biomarkers with low effects is estimated to be approximately 20%. All replicated biomarkers will be built into a prediction model that will be optimised and evaluated by cross-validation. The primary hypothesis is that the biomarker signature will be able to characterise the participant population into an IBD and a non-IBD group.

In the *prognostic utility study*, we expect a sample size of 256 IBD patients and a 10% event rate for severe IBD within 52 weeks.^32 33^ If we assume a 15% event rate for the biomarker positive group and a 5% event rate for the biomarker negative group, and anticipate an even 1:1 biomarker positive-to-negative distribution, approximately 80 patients in each group will increase the statistical power above the 90% threshold.

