### Prognostic factor research (the prognostic utility study)

The primary statistical analysis will be based on the proportion of participants experiencing severe IBD among biomarker-positive versus biomarker-negative patients. The efficacy of the prognostic biomarker(s) will be considered as the proportion of the patients with different disease outcomes among the biomarker-positive patients compared with the biomarker-negative patients. The associations of the suspected important molecular biomarkers with other variables will be tested with non-parametric tests: with Spearman’s rank correlation (rs) for continuous variables and the Wilcoxon rank-sum test or Kruskal-Wallis test, including a Wilcoxon-type test for trend across ordered groups where appropriate, for categorical variables.

Logistic regression models will be utilised with individual markers as the exposure variables and composite clinical severity as the outcome (dependent variable). The analyses will be adjusted simultaneously for sex, age and prescribed therapy. Potential interactions between biomarker status (positive/negative) and specific drug type will be evaluated too. Covariates comprise of various measures within genetics, transcriptomics, microbiomes and proteomics (see Biomarkers section). We will attempt to develop prediction models containing several conventional risk factors (ie, age, sex and type of drug therapy) with or without any novel biomarkers and calculate improvements in predictive ability using risk discrimination and reclassification measures. We will use a two-stage approach that allows for the examination of centre heterogeneity through the calculation of the C-index, a measure of risk discrimination and changes within each centre before pooling results.

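### For severe IBD, a C-index calculated within each of 11 centres and then pooled is poorly suited to about 26 expected events, or about 2.3 per centre

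*Protocol article*

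**What the plan says.** The protocol article, under Prognostic factor research, plans models with conventional risk factors, with and without novel biomarkers, and judges the gain by discrimination and reclassification. It then commits to a two-stage approach that permits "examination of centre heterogeneity through the calculation of the C-index, a measure of risk discrimination and changes within each centre before pooling results". The unit of the first stage is the centre, and both the C-index and its change are to be obtained there.

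The Setting section describes a "collaboration between gastroenterology departments in 11 Nordic hospitals". Under Statistical methods the authors write that "we expect a sample size of 256 IBD patients and a 10% event rate for severe IBD within 52 weeks". The patient number comes from two other statements in that section: cost and practical issues "restrict the sample size to approximately 800 patients, with an expected 80% participation rate", and "approximately 40% of a population referred with suspected IBD will have the diagnosis confirmed".

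The article does not give recruitment by centre, a minimum number of events for a centre to enter the first stage, or the weights for the second stage.

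**The concern.** A C-index compares patients who had the event with patients who did not. A centre without events has no such pairs and so no C-index. A centre with one or two events has a value that depends almost wholly on where those one or two patients happen to rank. The two-stage approach has two uses here, and sparse events threaten both.

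- **Reading heterogeneity.** If chance alone spreads the centre values widely, the first stage cannot separate centres that differ from centres that do not. The article lists patient heterogeneity across four countries among its limitations, so the question is a real one for this study.
- **Pooling.** The estimated standard error of a C-index depends on the estimate and shrinks towards zero as the estimate approaches 1. Inverse-variance weights based on such standard errors favour centres whose value is high by chance. The pooled C-index would then overstate discrimination, and the C-index is one of the measures by which the added value of a biomarker is to be judged.

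**Working it through.** **Inputs from the article:** 800 patients, 80% participation, 40% with confirmed IBD, a 10% event rate and 11 centres. **Assumptions:** equal centre sizes unless stated otherwise, and a true C-index of 0.70.

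**The plan's own figure.** 800 × 0.80 × 0.40 = 256 IBD patients, which reproduces the article. Events: 256 × 0.10 = 25.6.

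**Per centre.** 256 / 11 = 23.3 patients; 25.6 / 11 = 2.33 events.

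**Centres with too few events (binomial, p = 0.10).**
- No event: 0.9^23.3 = 0.086, so 11 × 0.086 = 0.95 centres are expected to have no C-index.
- At least one such centre: 1 − (1 − 0.086)^11 = 0.63.
- None or one event: 0.086 + 23.3 × 0.10 × 0.9^22.3 = 0.31, or about 3.4 of 11 centres.

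**Precision (Hanley-McNeil).** With m events and n non-events, variance = [C(1 − C) + (m − 1)(a − C²) + (n − 1)(b − C²)] / (mn), where a = C/(2 − C) and b = 2C²/(1 + C). At C = 0.70, a − C² = 0.0485 and b − C² = 0.0865.

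| Unit | m / n | Variance | SE |
|---|---|---|---|
| One centre | 2.33 / 20.9 | (0.21 + 0.064 + 1.725) / 48.7 = 0.0410 | 0.20 |
| One of four equal countries | 6.4 / 57.6 | (0.21 + 0.262 + 4.894) / 368.6 = 0.0146 | 0.12 |
| All patients | 25.6 / 230.4 | (0.21 + 1.192 + 19.836) / 5898 = 0.0036 | 0.06 |

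A centre's 95% interval is 0.70 ± 1.96 × 0.20, which runs from about 0.3 to the upper limit of 1.

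**Sensitivity to the sample size.** If all 800 took part, there would be 800 × 0.40 = 320 IBD patients and 32 events, or 2.9 per centre. The SE is then 0.18 and the chance of at least one centre without events is 41%.

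**Simulation.** Event probability 0.10, normally distributed scores, 11 centres. Centre sizes were either 23 to 24 each or an assumed unequal split from 5 to 60 (total 256).
- *Heterogeneity, equal sizes.* With no true difference, the lowest and highest centre values average 0.35 and 0.95 (SD between centres 0.19). Cochran's Q rejects in about 5% of runs when the true between-centre SD is 0.10, and about 15% when it is 0.15. Under the unequal split the results are similar, and about 2.3 centres have no C-index.
- *Inverse-variance pooling with DeLong standard errors.* About 3.5 of 11 centres have no usable standard error (5.2 if unequal). The mean pooled C-index is 0.78 (0.76 if unequal), and the 95% interval covers the true value in 44% (58%) of runs.
- *Pooled within-centre pairs.* All event/non-event pairs from the same centre are put into one proportion. The mean is 0.70 and the SD about 0.06 under both splits.

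**The case against.** The strongest reply is that the article does not prescribe the method that fails. It names no weights, no standard-error formula and no heterogeneity test, and it speaks only of examining heterogeneity. Such details commonly belong in a statistical analysis plan, which the article promises before any analysis. This stands as far as the bias goes: the bias is conditional on inverse-variance weights with empirical centre-specific standard errors, and other weights give a smaller bias or none. It does not remove the heterogeneity problem, because obtaining the C-index and its change centre by centre is what the article fixes, and no choice of weights makes 2.3 events informative.

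A reader might infer that the two-stage approach cannot work at all, or that the centre values are mostly undefined. The figures do not support that. Only about one of 11 equal-size centres is expected to have no C-index; the others are defined but very imprecise. A pooled within-centre C-index with suitable weights is estimable and nearly as precise as one from all patients.

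A reader might also infer that the study's assessment of added value is lost. It is not: reclassification measures are planned too, and the primary prognostic analysis compares proportions between biomarker groups. Nor does unequal recruitment make everything worse. In the assumed split more centres are lost, but the bias is smaller and the coverage better.

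On scope, the C-index sentence names no outcome. For diagnosis, 256 / 11 = 23 IBD and 384 / 11 = 35 non-IBD patients per centre would be workable. The sentence stands in the prognostic section, however, so severe IBD is the natural reading.

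Finally, the alternative has limits of its own. Centres without events contribute no pairs to it either, and a country-level estimate with an SE of about 0.12 is still imprecise.

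**Conclusion.** The point holds for the severe-IBD outcome, as a weakness in a secondary analysis. With about 2.3 events per centre and a centre SE of about 0.20, centre heterogeneity in discrimination, or in its change, cannot be read from the planned first stage. If the second stage uses inverse-variance weights with DeLong standard errors, the pooled C-index is biased upward, to about 0.76 to 0.78 for a true 0.70, and its interval covers far too seldom.

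The patient number, event rate and number of centres are the article's own. Centre sizes, the true C-index and the pooling weights are assumptions. The precision finding survives full enrolment of 800 and an unequal split; the size of the bias depends on the weights and the standard-error formula. The documents do not support the broader conclusion that pooling across centres is impossible or that the main prognostic result is affected.

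**What to change.** In the statistical analysis plan, for the severe-IBD outcome:

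1. Replace the centre-by-centre estimates with a single centre-stratified C-index, and its change between models with and without the biomarker, from pooled within-centre pairs. Give a bootstrap confidence interval.
2. Report how many centres had no events and so contributed no pairs.
3. Show differences between the four countries descriptively, by leaving out one country at a time. State that about 6 events per country (25.6 / 4 = 6.4 if equal) cannot support a heterogeneity test.

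This costs analysis wording only; it needs no further patients or data. The downside is that there will be no estimate of heterogeneity between hospitals, but the expected events could not have provided a usable one.

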### Patient and public involvement

The NORDTREAT project has evolved in collaboration with patient research partners (PRPs) from the Danish Colitis-Crohn’s Association, the Norwegian Mage-tarmforbundet, the Swedish Mag- och tarmförbundet and from Icelandic patient representatives ensuring implementation of patient perspectives in aspects such as, for example, research aims and outcomes. The PRPs were involved before the formal project start (adding value in the design of the study) and they are continuously informed on study progress. Overall, the PRPs add value in the project conduct through their engagement in the Patient Advisory Council (online supplemental
appendix
3) increasing knowledge-sharing, awareness on the project and research comprehensiveness.

10.1136/bmjopen-2023-083144.supp3Supplementary data

When reporting the *diagnostic test accuracy study*, we will adhere to the STARD guideline^34^ and the TRIPOD statement,^35^ and when reporting the *prognostic utility study*, we will apply the STROBE^36^ as well as the TRIPOD statement.^35^ Before any analyses are initiated, an elaborated statistical analysis plan indicating explicit figures and tables will be provided.

### Project organisation

The NORDTREAT partnership builds on extensive professional experience, a strong track record of collaborative clinical projects and participation in a number of European and global consortia (eg, the IBD Character Consortium, the SYSCID Consortium and the International IBD Genetic Consortium).

The NORDTREAT cohort study is conducted in parallel and as part of the NORDTREAT trial (a biomarker-stratified randomised controlled trial (RCT)). The aim of the NORDTREAT RCT is to demonstrate that personalised therapy can be applied to patients with IBD, by assessing if a top-down treatment can improve clinical outcomes in IBD patients with an increased risk of poor disease course (https://clinicaltrials.gov/ct2/show/NCT05180175).

The operational organisation of the NORDTREAT study is highlighted in online supplemental

appendix
3)).

Finally, the *Executive Committee* (members listed in online supplemental
appendix
3) is responsible for project coordination and management during the research project’s preparation, operation and finalisation. Biweekly online meetings are conducted, ad-hoc meetings when necessary and face-to-face meetings are held twice a year.

### Perspectives

Substantial differences exist between patients suspected of IBD when comparing symptoms, onset, prognosis and treatment, which makes a one-size-fits-all approach insufficient. With current knowledge and clinical methodologies, the diagnosis and prognosis of IBD is challenging without invasive investigations. However, newly identified biomarkers may have implications for future disease management, as they could be used to differentiate patients with IBD and patients with other comparable gastrointestinal symptoms or predict disease outcomes. If we succeed in identifying diagnostic or prognostic biomarkers of IBD, substantial improvement will be given to IBD treatment, including reduced side-effects and complications, increased quality of life for patients and their relatives and a reduced socioeconomic burden on society. Relevant findings with potential clinical value will be evaluated and replicated in other prospective cohorts if possible.

### Ethics and dissemination

The study is approved by the Ethics Committee (DK: S-20200051, v1.4, 16.10.2021; IS: VSNb2021070006/03.01, NO: 193064; SE: DNR 2021-05090) and the Danish Data Protecting Agency (20/54594). The procedures followed are in accordance with the ethical standards of the responsible committee on human experimentation (institutional and national) and with the Helsinki Declaration of 1975 with later amendments.

The target journal for the primary outcome will be a gastroenterology medical journal. Subsequently, other hypotheses will be tested, and manuscripts will be prepared with the intention of submitting to specialised journals in microbiome research, immunology, genetics, nutrition and gastroenterology. In addition to the scientific reporting, key findings with translational implications will be communicated to health professionals, patient organisations, public health policymakers and the public through various media and news activities. When disseminating the results, we will apply the recommendations of the *International Committee of Medical Journal Editors (ICMJE)*.
